### Statistical considerations

Statistical methods are described in detail for the primary mortality and AMR outcomes, which will involve intention-to-treat analyses.

#### Primary outcome definitions

The primary mortality outcomes are defined as:Under-5 mortality rate (U5MR, deaths per 1000 live births) assessed by pregnancy history after 2 years of distributions, comparing the intervention and delayed armsUnder-5 mortality rate (U5MR, deaths per 1000 live births) assessed by pregnancy history after 4 years of distributions, comparing the continue and stop arms

We will calculate the U5MR at the CSI level as the cumulative probability of mortality by age 60 months using a synthetic cohort approach from pregnancy history records [26].

The primary AMR outcomes are defined as:Prevalence of macrolide-resistant pneumococcus from nasopharyngeal swabs in children 1–59 months old after 2 years of distribution, comparing the intervention and delayed armsPrevalence of macrolide-resistant pneumococcus from nasopharyngeal swabs in children 1–59 months old after 4 years of distributions, comparing the continue and stop armsLoad of genetic determinants of resistance to macrolides from rectal swabs in children 1–59 months old after 2 years of distributions, comparing the intervention and delayed armsLoad of genetic determinants of resistance to macrolides from rectal swabs in children 1–59 months old after 4 years of distributions, comparing the continue and stop arms 

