The initial design includes the following specific aims:Specific Aim 1—Mortality: to evaluate the effectiveness of azithromycin MDA to reduce under-5 mortality every 2 years in a real-world program setting.Trial 1: In the first 2 years of the trial, we will compare under-5 mortality in CSIs randomized to azithromycin MDA or delayed treatment.Trial 2: In the second 2 years of the trial, we will compare under-5 mortality in CSIs randomized to stop or continue azithromycin MDA.Specific Aim 2—Antimicrobial resistance:To compare the prevalence of macrolide-resistant *Streptococcus pneumoniae* from nasopharyngeal swabs in population-based samples of children 1–59 months old every 2 years.i.Trial 1: In the first 2 years of the trial, we will compare the prevalence of macrolide resistance in CSIs randomized to azithromycin MDA or delayed treatment.ii.Trial 2: In the second 2 years of the trial, we will compare the prevalence of macrolide resistance in CSIs randomized to stop or continue azithromycin MDA.iii.At year 4, we will compare the prevalence of macrolide resistance in CSIs randomized to have had 4 years of azithromycin MDA or 2 years (continue vs original delayed then treated)To compare the load of genetic determinants of resistance to macrolides from rectal swabs in children 1–59 months old every 2 years.i.Trial 1: In the first 2 years of the trial, we will compare the load of macrolide resistance determinants in CSIs randomized to azithromycin MDA or delayed treatment.ii.Trial 2: In the second 2 years of the trial, we will compare the load of macrolide resistance determinants in CSIs randomized to stop or continue azithromycin MDA.iii.At year 4, we will compare the load of macrolide resistance determinants in communities randomized to have had 4 years of azithromycin MDA or 2 years (continue vs original delayed then treated)Specific Aim 3—Implementation:To evaluate equity of treatment coverage and identify barriers, facilitators, and implementation strategies to increase coverage.To map the intervention delivery process and identify the flow of inputs required to achieve high treatment coverage.To determine program costs, cost-effectiveness, and variations in implementation strategies that affect costs.To monitor the fidelity of the administration of the intervention to the protocol.

This protocol was prepared according to SPIRIT reporting guidelines [7].

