### Setting, timeline, and participants

All accessible and secure regions in Niger will be progressively included in the program over a 2-year period. Program activities will begin in the Dosso, Tahoua, and Maradi regions in mid-2024, in the Zinder region at the end of 2024, and in the remaining regions in 2025 and 2026 (Fig. 2). The first 4 regions launching in 2024 are expected to encompass approximately 75% of the target population and will be included in the trials and monitoring activities. We anticipate reaching approximately 3.3 million children and delivering 15.4 million doses of azithromycin over the 4-year period in the overall program (Table 2).

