**Fig. 2 Fig2:**
[figure not shown]
Implementation rollout plan. Map of the regions of Niger colored according to the progressive scale-up plan. Borders indicate the 7 regions in Niger plus the capital of Niamey, which is not included in the scale-up. All regions are included in the national program and the Dosso, Tahoua, Maradi, and Zinder regions are included in the trial. Phase 1 is expected to begin in the second and third quarters of 2024. Phase 2 is expected to begin in the fourth quarter of 2024. Phase 3 is expected to begin in the second quarter of 2025. and Phase 4 is expected to begin in the second quarter of 2026

**Table 2 Tab2:** Timeline and impact of progressive national scale-up of azithromycin mass administration in Niger. Phase 1 is expected to begin in the second and third quarters of 2024. Phase 2 is expected to begin in the fourth quarter of 2024. Phase 3 is expected to begin in the second quarter of 2025. and Phase 4 is expected to begin in the second quarter of 2026

Region	Trial or program	Start time	Districts	CSIs	MDAs^a^	Estimated eligible children 1–59m^b^	Estimated number of delivered overall^c^
Dosso	Both	Phase 1	8	192	7	431,461	2,416,182
Tahoua	Both	Phase 1	13	267	7	670,002	3,752,011
Maradi	Both	Phase 1	9	216	7	665,826	3,728,626
Zinder	Both	Phase 2	11	219	6	731,986	3,513,533
Agadez	Program only	Phase 3	7	92	5	67,298	269,192
Tillabéri	Program only	Phase 4	13	270	3	585,215	1,404,516
Diffa	Program only	Phase 4	6	72	3	129,642	311,141
**Total**			**67**	**1328**	**38**	**3,281,430**	**15,395,200**

*CSI* Centre de Santé Integré (primary health center), *m* months, *MDA* mass drug administration

^a^Assuming twice yearly MDA

^b^Population estimates including rural and peri-urban communities, produced by the Institute for Disease Modeling (IDM)

^c^Using IDM population estimates and assuming 80% coverage

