#### Analysis

The primary analysis for U5MR will be to compare the proportion of children who die before age 60 months between the two arms. The prior likelihood for mortality will be estimated using cluster-level data from the AVENIR I trial, using methods similar to the likelihood estimation [3]. We will model CSI-level U5MR using a generalized linear regression model with terms for treatment arm and baseline U5MR. CSIs should be of similar size, but if we find there are large differences in size, then we will consider weighting the regression by the number of measurements in each CSI. We will estimate the likelihood of the data from the fitted regression model. Note that the MOH committee and DSMC will review and approve the prior used past the second year of the trial, with options including incorporation of new results outside of AVENIR I and II, as well as down-weighting the prior from AVENIR I over time.

To estimate the posterior, beginning with the maximum likelihood estimate of all parameters obtained by the generalized linear model, we will choose particular values of the treatment effect b. For each such value, we maximize the likelihood with respect to the other parameters, yielding the profile likelihood function with respect to the single parameter b. We will multiply the profile likelihood by the prior to obtain the posterior distribution, normalized to ensure the posterior likelihood sums to 1. We will derive Bayesian credible intervals from the posterior derived in this way. Specifically, we will report the 95% central coverage interval and the estimated median. We will also estimate the probability of the null hypothesis under the posterior likelihood, and its complement (the probability MDA reduces the U5MR). Subgroup analyses for U5MR include region, child age, child sex, and community distance to the CSI. Note that for analyses of the second trial comparing the continue vs stop arms, the first 6 months will be excluded from analyses to allow for a washout period to account for lingering effects from prior treatment.

The Bayesian credible intervals of the U5MR will also be used to compare the measured mortality rate against the Sustainable Development Goal (SDG) targets (a secondary outcome). We will estimate the probability that the U5MR is at or below the SDG target using the area of the posterior distribution that falls at or below the SDG target.

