## Trial status

This manuscript describing the AVENIR II protocol was developed based on the official study protocol version 15, which was last revised on 2 October 2025. Recruitment began in June 2024 and is expected to be completed in May 2028.

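### Trial 2 and the year-4 resistance outcomes are defined after four years of distributions, but Table 2 plans only 7 six-monthly rounds (6 in Zinder)

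*Protocol article*

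**What the plan says.** Primary outcome definitions sets the Trial 2 mortality outcome as "assessed by pregnancy history after 4 years of distributions, comparing the continue and stop arms". The resistance outcomes are measured "in children 1–59 months old after 4 years of distributions, comparing the continue and stop arms". Specific Aim 2 adds a year-4 comparison of "CSIs randomized to have had 4 years of azithromycin MDA or 2 years". The design overview places Trial 2 in the second 2 years, and Interventions sets one round every 6 months.

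Table 2 gives 7 rounds each for Dosso, Tahoua and Maradi, which start in Q2-Q3 2024, and 6 for Zinder, where "Phase 2 is expected to begin in the fourth quarter of 2024". Its footnote reads "Assuming twice yearly MDA". Setting, timeline, and participants cites this table for "delivering 15.4 million doses of azithromycin over the 4-year period in the overall program".

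For Trial 2, Analysis states that "the first 6 months will be excluded from analyses to allow for a washout period". Censuses are only approximately every 2 years. Trial status says "Recruitment began in June 2024 and is expected to be completed in May 2028". Sample size and power assumes that the Trial 1 calculations also apply to Trial 2.

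**The concern.** Trial 2 is meant to inform the ministry on stopping the program, a question for which the article says no guidance exists. That needs a continue arm that is still being treated while deaths are counted and swabs taken. If distribution ends in mid-2027 and the final measurement falls near month 48, neither arm has had a round for some time by then. The mortality and resistance contrasts would be pulled toward zero, and a small difference could be mistaken for evidence that stopping makes little difference. If measurement comes earlier instead, Trial 2 has less follow-up than its definition implies. In both cases the described exposure is not the one that the dose plan delivers.

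**Working it through.** **1. Reproduce Table 2.** Doses = eligible children × 0.80 × rounds.
- Dosso: 431,461 × 0.80 × 7 = 2,416,182
- Tahoua: 670,002 × 0.80 × 7 = 3,752,011
- Maradi: 665,826 × 0.80 × 7 = 3,728,626
- Zinder: 731,986 × 0.80 × 6 = 3,513,533

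The three program-only rows also reproduce, and the total is 15,395,200 as stated. The 7 and 6 are therefore the counts behind the dose total, not misprints.

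**2. Date of the last round.** Last round = 6 × (rounds − 1) months after the region's first.
- Phase 1 regions: 6 × 6 = month 36, Q2-Q3 2027
- Zinder: 6 × 5 = month 30, Q2 2027
- Agadez (5 rounds from Q2 2025): month 24, Q2 2027
- Tillabéri and Diffa (3 rounds from Q2 2026): month 12, Q2 2027

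All rows end together, which suggests one planned end of distribution.

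**3. Rounds per arm**, counting each region from its own start.
- Trial 1: months 0, 6, 12, 18, so 4 v 0.
- Trial 2, Phase 1 regions: months 24, 30, 36, so 3 v 0.
- Trial 2, Zinder: months 24, 30, so 2 v 0.
- Maradi, continue v originally delayed: 7 v 3 rounds, where 4 v 2 years would be 8 v 4.

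**4. Analysed window.** It starts at month 30 after the washout. A month is beyond the interval if it falls more than 6 months after the last continue-arm round, that is after month 42 (Zinder 36).

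| Final census | Phase 1 regions | Zinder |
|---|---|---|
| Month 48 on the Phase 1 calendar (Zinder month 42) | 6 of 18 months beyond (one third) | 6 of 12 (one half) |
| Month 48 on each region's own clock | 6 of 18 (one third) | 12 of 18 (two thirds) |
| 6 months after the last round | 0 of 12 | 0 of 6 |

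In the last row, 3 × 12 + 6 = 42 region-months remain, against 4 × 18 = 72 intended (58%).

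**5. Resistance (Maradi only).** A month-48 swab falls 48 − 36 = 12 months after the last round. A year-2 swab falls 24 − 18 = 6 months after one.

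**6. Power, illustration only.** The standard error is 16.6 × √(2/100) = 2.35, and a difference of 6.6 gives 80% power, as stated. Suppose the effect is proportional to time within 6 months of a round:
- Census at month 48 on each region's clock: (3 × 12 + 6)/72 = 58% covered, effect 3.85, power about 37%.
- Census closing in May 2028 (about 16 analysed months in Phase 1 regions, 12 in Zinder): 42/(3 × 16 + 12) = 70% covered, effect 4.62, power about 50%.

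**7. If 8 rounds are meant.** One more round in the Phase 1 regions adds 0.80 × 1,767,289 = 1,413,831 doses. Each extra Zinder round adds 0.80 × 731,986 = 585,589. The total becomes 17,394,620 (Zinder 7 rounds) or 17,980,209 (Zinder 8), against 15,395,200.

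**The case against.** Table 2 is a national dose forecast, not the trial schedule. Table 1 marks each round and is not shown here, and no visible sentence says that distribution stops before Trial 2 follow-up ends. The reference to 4 years may be a loose name for the last measurement. Census timing is approximate, and a census of 200 catchment areas must begin well before any closing date. These points stand, and they mean that an untreated gap is not established. They do not remove the contradiction. Whatever Table 1 shows, a dose total said to cover the 4-year period uses 7 and 6 rounds, while the outcomes assume four years of six-monthly rounds.

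The resistance section says that health workers complete treatment for the round after sampling, which ties swabs to a round. That weakens any claim that year-4 swabs will come 12 months after treatment. But Table 2 has no Maradi round near month 48, so this too needs reconciling.

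A reader might infer that most of the analysed period has neither arm treated. The documents do not support that. Even with a month-48 census, Phase 1 regions are within one dosing interval for 12 of 18 months. The two-thirds figure for Zinder needs follow-up to Q4 2028, which sits badly with the May 2028 date (although what recruitment means there is not defined).

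Nor can one conclude that power is 37-50%. That range assumes that the effect vanishes at exactly 6 months, treats the detectable 6.6 as the true effect, and uses a t-test although the primary analysis is a posterior with an AVENIR I prior.

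**Conclusion.** The inconsistency holds: the outcome definitions imply 8 rounds and the dose plan contains 7, or 6 in Zinder. One side has to change.

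- If Table 2 is right, exposure is 3 v 0 rounds in Trial 2 (Zinder 2 v 0), and 7 v 3 in the Maradi comparison labelled 4 v 2 years. A census near month 48 or May 2028 leaves up to about one third of the Phase 1 window and about one half of Zinder's beyond one dosing interval, with Maradi swabs up to about 12 months after the last round. The contrast is diluted by an amount that depends on unknown waning; slower waning makes it smaller. A census about 6 months after the last round avoids this but leaves 12 analysed months (Zinder 6) rather than 18.
- If 8 rounds are planned, the dose total is understated by about 2.0 to 2.6 million.

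Under the Table 2 counts, carrying Trial 1's power over to Trial 2 is not justified at either census date. That Trial 2 will wrongly suggest stopping is harmless is a risk under one timing, not a demonstrated consequence. Confidence is moderate, because the schedule figure is not available.

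**What to change.** Reconcile the design overview, Specific Aims, Setting and Table 2, Randomization unit and monitoring sample, and Primary outcome definitions on the number of rounds and the month of final measurement. Which schedule is correct is for the sponsor to settle. State the Trial 2 and year-4 contrasts as rounds received per arm, by region.

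If the Table 2 counts stand:
- end the primary Trial 2 mortality window in each region no later than one dosing interval after the last continue-arm round, or at the census if earlier;
- take year-4 swabs at the same interval after the last continue-arm round as at year 2;
- restate Trial 2's precision for that window and exposure.

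If more rounds are planned, correct the round counts and dose total in Table 2 and the text.

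For mortality the cost is wording in the protocol and analysis plan, provided that the pregnancy histories date deaths well enough to cut the window. For resistance, the swab date may have to be moved. The price is a shorter Trial 2 window and a less favourable stated precision.

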#### Analysis

The primary analysis for U5MR will be to compare the proportion of children who die before age 60 months between the two arms. The prior likelihood for mortality will be estimated using cluster-level data from the AVENIR I trial, using methods similar to the likelihood estimation [3]. We will model CSI-level U5MR using a generalized linear regression model with terms for treatment arm and baseline U5MR. CSIs should be of similar size, but if we find there are large differences in size, then we will consider weighting the regression by the number of measurements in each CSI. We will estimate the likelihood of the data from the fitted regression model. Note that the MOH committee and DSMC will review and approve the prior used past the second year of the trial, with options including incorporation of new results outside of AVENIR I and II, as well as down-weighting the prior from AVENIR I over time.

To estimate the posterior, beginning with the maximum likelihood estimate of all parameters obtained by the generalized linear model, we will choose particular values of the treatment effect b. For each such value, we maximize the likelihood with respect to the other parameters, yielding the profile likelihood function with respect to the single parameter b. We will multiply the profile likelihood by the prior to obtain the posterior distribution, normalized to ensure the posterior likelihood sums to 1. We will derive Bayesian credible intervals from the posterior derived in this way. Specifically, we will report the 95% central coverage interval and the estimated median. We will also estimate the probability of the null hypothesis under the posterior likelihood, and its complement (the probability MDA reduces the U5MR). Subgroup analyses for U5MR include region, child age, child sex, and community distance to the CSI. Note that for analyses of the second trial comparing the continue vs stop arms, the first 6 months will be excluded from analyses to allow for a washout period to account for lingering effects from prior treatment.

The Bayesian credible intervals of the U5MR will also be used to compare the measured mortality rate against the Sustainable Development Goal (SDG) targets (a secondary outcome). We will estimate the probability that the U5MR is at or below the SDG target using the area of the posterior distribution that falls at or below the SDG target.

The primary analysis for resistance outcomes from community-based collection of nasopharyngeal (NP) swabs will be to compare the proportion of macrolide-resistant pneumococcal isolates between the two arms. If the laboratory is not able to grow pneumococcal isolates in at least 30% of the samples, we will use DNA testing instead.

The primary analysis for the community-based collection of rectal swabs will compare the community-level load of macrolide-resistant genetic determinants between the two arms. For both sets of samples, secondary analyses examining resistance in other classes of antibiotics, other age groups, and among individual antibiotic resistance genes will be conducted similarly.

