### Randomization, adaptation, and masking

#### Randomization unit and monitoring sample

The randomization unit for this trial is the CSI, which is a primary health care center with an average catchment area of approximately 20 communities (*grappes)*, each of which includes an average of approximately 100 children under 5. A random sample of 200 CSIs eligible for the program will be selected for participation in the trials as a stratified sample of 50 CSIs from each of the four regions launching the program in year 1: Dosso, Tahoua, Maradi, and Zinder. Trial 1 will include this initial sample of 200 CSIs, which will be randomized 1:1 to receive the intervention or to receive delayed treatment. After 2 years, the 100 delayed CSIs will be treated by the program. For Trial 2, we will select another random sample of 200 CSIs from among those previously treated, again stratified by region. Note that the sample sizes included in Trial 2 are subject to the adaptation as described in the next section.

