#### Adaptation

Allocation probabilities for AVENIR II will adapt from the AVENIR I trial based on 1–59-month mortality using the following algorithm [3]. Given all outcome measurements available through the primary endpoint for AVENIR, we will fit a negative binomial model to the data from the 1–59-month and placebo arms. From the model, we will estimate the log mortality rate for each arm and its corresponding standard error. We will then draw 10,000 replicates of log mortality rates from the estimated distributions, assuming they are normally distributed, and in each draw of the joint distribution, we will determine which arm has the lowest mortality rate. We will estimate the probability that each arm has the lowest mortality rate as the proportion of 10,000 replicates in which the arm has the lowest mortality rate. In AVENIR II, there will be no tempering of allocation probabilities because we have sufficient information to be protected from uninformed swings in allocation.

The adaptive algorithm will include a minimum probability for the delayed and stopping arms to enable continued comparison to untreated groups while ensuring the majority retain access to treatment based on statistical power and expert opinion. The preliminary value is 0.10, which was used in the AVENIR I algorithm and confirmed by a survey of expert opinion. As we anticipate 894 total CSIs in Dosso, Tahoua, Maradi, and Zinder regions, a 10% allocation would represent 90 CSIs in the delayed group, or approximately 23 CSIs per region (rounded to whole numbers). To account for potential exclusions due to accessibility, we will include 25 delayed CSIs per region with an equal number of treated CSIs per region, for a total of 50 CSIs per region and 200 CSIs in the monitoring population of the trials (Fig. 1). The adaptation will be updated after Trial 1 to inform Trial 2. Allocation sequences will be generated by the UCSF biostatistician in R (R Foundation for Statistical Computing).

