### Outcome assessments

#### Mortality

The primary mortality outcome will be defined as the under-5 mortality rate (U5MR, deaths per 1000 live births) as assessed by pregnancy history. A population-based census will be conducted in 50 randomly selected CSIs per region in Dosso, Tahoua, Maradi, and Zinder at baseline (25 per arm) and then approximately every 2 years. Trained data collectors will visit each household in the study area to obtain verbal informed consent for participation. Household GPS coordinates and basic demographic data for the head of household and women of childbearing age (15–49 years old) will be collected. Full pregnancy histories will be conducted using procedures similar to those outlined in the Demographic and Health Survey 8 [10, 11]. Beginning with the first pregnancy, each woman will be asked about each pregnancy she has experienced, and pregnancy outcomes will be recorded for each. Current vital status, age, and sex will be recorded for all live births.

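### Region is the design stratum, yet the primary U5MR model leaves it out, at a cost in precision that is probably modest

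*Protocol article*

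**What the plan says.** Region is built into the design. Under Randomization unit and monitoring sample, Trial 1 uses "a stratified sample of 50 CSIs from each of the four regions launching the program in year 1", 200 in all, "which will be randomized 1:1 to receive the intervention or to receive delayed treatment". The Adaptation section fixes the split within region: "we will include 25 delayed CSIs per region with an equal number of treated CSIs per region". The Mortality section repeats it for the census, which is done "at baseline (25 per arm) and then approximately every 2 years".

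For Trial 2 the article plans "another random sample of 200 CSIs from among those previously treated, again stratified by region". That sentence describes how CSIs are sampled. It does not state a within-region allocation, and the Trial 2 numbers may change with the adaptation.

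The primary analysis is in the Analysis section: "We will model CSI-level U5MR using a generalized linear regression model with terms for treatment arm and baseline U5MR". Values of the arm effect are profiled from this model, multiplied by the AVENIR I prior and normalised to give the posterior and its 95% interval. Region enters the mortality analysis in one other place only: "Subgroup analyses for U5MR include region, child age, child sex, and community distance to the CSI". The opening of Statistical considerations presents these as the detailed methods for the primary outcomes, so the list of terms reads as the chosen model and not as an omission left for later.

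**The concern.** When arms are balanced 25:25 in every region, differences between regions cancel out of the arm comparison. A model without region does not know this. It counts whatever regional variation baseline U5MR leaves unexplained as ordinary residual noise. The arm estimate stays unbiased, but its standard error is overstated.

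Two things follow. The likelihood for the arm effect is too flat, so the interval is wider than the design warrants and the probability of benefit is pulled in a conservative direction. And because the posterior is likelihood times prior, a likelihood that is too flat gives the AVENIR I prior more weight relative to the new programme data. The trial exists to measure real-world effect afresh, and the Discussion already warns that power may fall short, so precision that the design has paid for is worth keeping.

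**Working it through.** **1. The plan's own figure.** Inputs from the U5MR part of Sample size and power: 100 CSIs per arm, SD 16.6, alpha 0.05 (taken as two-sided), t-test of cluster means.
- 80% power: (1.960 + 0.842) × 16.6 × √(2/100) = 6.58; with the noncentral t, 6.61. The plan states 6.6.
- 90% power: (1.960 + 1.282) × 16.6 × √(2/100) = 7.61; with the noncentral t, 7.65. The plan states about 7.7.

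The figures reproduce and are not in dispute. They use no baseline or region adjustment.

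**2. Effect of adding region when baseline U5MR is already in the model.** The article gives no regional U5MR and no between-region variance, so the following are assumptions: a linear model for CSI-level U5MR; total CSI-level variance equal at both surveys and set to 1; a share f lying between regions; regional differences the same at baseline and follow-up; and a within-region correlation ρ between baseline and follow-up.
- Overall baseline/follow-up correlation: r = f + (1 − f)ρ
- Residual variance with arm and baseline only: 1 − r²
- Residual variance with region added: (1 − f)(1 − ρ²)
- Width ratio (with region / without): √[(1 − f)(1 − ρ²) / (1 − r²)]

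Example, f = 0.30 and ρ = 0.3: r = 0.30 + 0.70 × 0.3 = 0.51; 1 − 0.51² = 0.7399; 0.70 × 0.91 = 0.637; √(0.637/0.7399) = 0.928.

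| f | ρ = 0 | ρ = 0.3 | ρ = 0.6 | interval narrows by |
|---|---|---|---|---|
| 0 | 1.000 | 1.000 | 1.000 | 0% |
| 5% | 0.976 | 0.987 | 0.994 | 1–2% |
| 10% | 0.953 | 0.974 | 0.988 | 1–5% |
| 20% | 0.913 | 0.950 | 0.976 | 2–9% |
| 30% | 0.877 | 0.928 | 0.964 | 4–12% |

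A simulation of four regions with 25:25 allocation, 1,500 runs per cell, agrees with these ratios to about 0.001. Where regional variance was present, nominal 95% intervals covered about 95–97% without region and about 95% with it.

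**3. Weight of the prior.** Information goes as the square of the width ratio. At f = 20%, ρ = 0: 0.913² = 0.83, so omitting region understates the data's precision by about 17%. At f = 10%, ρ = 0.6: 0.988² = 0.976, about 2%. At the extreme corner, f = 30% and ρ = 0: 0.877² = 0.77, about 23%.

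**4. Cost.** The stated model has three parameters, leaving 200 − 3 = 197 residual degrees of freedom. Three region indicators leave 194.

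**5. Confounding.** Suppose one region loses 10 CSIs in each arm and the others none. Each arm keeps 75 + 15 = 90 CSIs, and that region makes up 15/90 of both. Loss that is unequal across regions but equal by arm therefore leaves the arms balanced on region. Imbalance needs loss, or allocation, that differs by arm within regions.

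**The case against.** The strongest reply is that nothing here is invalid. The estimate is unbiased, coverage is at or slightly above nominal, and the direction of error is cautious. Baseline U5MR is measured in the monitored CSIs and carries much of any lasting regional difference, so the design is not simply ignored. The size is assumed, and zero is possible. The reported interval includes the AVENIR I prior, which shrinks any gain. A separate analysis plan, not shown, may already include region. All of this stands except the last: the article names the model terms, so the comment is fair against this text.

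Three stronger readings are tempting, and the article does not support them.
- A reader might apply √(1 − f) directly to the plan's 6.6, getting 6.3, 5.9 and 5.5 for f of 10%, 20% and 30%, a 5–16% gain equivalent to 11–43% more CSIs. That takes baseline U5MR to explain none of the regional difference and rescales a figure from an unadjusted t-test. The article does not say whether the SD of 16.6 contains between-region variance; if it does not, a region term would help to protect 6.6 rather than lower it.
- A reader might infer that unequal loss across regions confounds the comparison. As shown above, it does so only if loss differs by arm within regions. The Missing data section also plans a weighted sensitivity analysis above 15% loss, and its candidate baseline characteristics could include region.
- A reader might cite Zinder's 6 planned MDAs against 7 elsewhere. Those are whole-programme counts in Table 2, not Trial 1 exposure, and the start phase is set by region, so it is balanced between arms.

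**Conclusion.** The point holds as one of efficiency. The primary U5MR model omits the factor on which CSIs are sampled in both trials and allocated in Trial 1. Under balanced allocation this causes no bias. It leaves the likelihood somewhat too flat, the interval somewhat too wide and the prior slightly too influential.

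For a regional share of 0–30% of CSI-level variance, the likelihood-based interval would narrow by roughly 0–12%, before dilution by the prior. That range assumes that regional differences persist from baseline and that the within-region correlation is 0 to 0.6. If regional differences arose only after baseline, the gain could approach 16% at a 30% share; if no regional variance remains after baseline adjustment, it is nil.

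For Trial 2 the article states regional stratification of the sample only. If adaptation or loss there made the arm ratio differ between regions, a region term would also guard against confounding.

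**What to change.** Add region (four levels) as a fixed effect to the primary U5MR model in both trials. The profile likelihood and posterior then inherit it. State in the Analysis section that the model's terms are arm, baseline U5MR and region, and name region among the covariates considered for the inverse-probability-of-censoring weights.

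The cost is three degrees of freedom and one line of text. Region is known for every CSI and is already used for subgroups, so no new data are needed and the sample size is unaffected.
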